### Ethics and Governance

Individual patient consent will be requested at entry by the recruiting clinician. All patients who fulfill the inclusion criteria will be given detailed information by a qualified researcher both verbally and in the form of a patient information sheet. Patients will be able to withdraw consent at any time during the study. Patients may also be withdrawn from the study for medical reasons.

Permission and approval for the proposed research will be requested using the relevant procedures for ethical review of studies of NHS patients in the United Kingdom. The protocol will be reviewed by an NHS Research Ethics Committee, overseen by the UK Health Research Authority. Local research and development approval will also be obtained from each participating center.

The chief investigator will be responsible for supervising the conduct of the research and for protecting the rights, safety, and welfare of the participants enrolled in the study. Principal investigators will be identified at each participating site to ensure that the research activities are conducted in an ethical manner and in accordance with UK regulations, institutional policies, and good clinical and research practice.

### Safety and Adverse Incidents

All adverse events will be recorded and acted on by a qualified member of staff (eg, a nurse under the supervision of the clinician). The SeHCAT test is standard practice and is a safe test that has been in use in the United Kingdom for more than 30 years. The SeHCAT radiolabeled synthetic bile acid is licensed and approved for use in the United Kingdom. The test involves exposure to a low dose of ionizing radiation. All procedures will comply with ARSAC regulations and patients will be given radiation protection instructions both verbally and in writing. The BAS drugs to be prescribed are licensed and used in standard practice, and will be used in full compliance with the licensed indication.

### Study Committees

A multidisciplinary Study Management Group will be responsible for running the study on a day-to-day basis and will include a manager, chief investigator, clinicians, and statisticians. A Study Steering Committee will take major decisions, such as changing the protocol, and will include members who are not involved with the running of the study. A Data and Safety Monitoring Committee will be established and will consist of at least 3 independent members, one of whom will be a clinical specialist and one a statistician. This committee will be responsible for assessing recruitment data and study conduct and the monitoring of adverse events. The research team will include external independent members, including a patient representative on the committees, to aid the team in making unbiased decisions free from financial, personal, or professional pressure.

## Results

Funding is currently being sought to carry out this proposed research.

## Discussion

### Strengths

The SeHCAT test for diagnosis of BAM has been in common use in UK nuclear medicine centers for more than 30 years. An evidence-based assessment of the accuracy of the SeHCAT test is overdue. This research is seen as a priority by the National Institute for Health and Care Excellence in the United Kingdom [18], who funded the recent prospective study of UK centers [6] and the development of this protocol.

Chronic diarrhea is a debilitating condition that is not only physically unpleasant to endure, but impacts on social engagement and quality of life. Improving diagnostic accuracy in the prediction of BAM should help lead to optimization of treatment for those patients whose diarrhea is linked to this condition and clinicians will be able to advise patients with greater confidence.

The recent UK review [4] and survey [6] suggest that the timing is currently optimal for conducting the proposed research. Up-to-date contextual baseline data are available and UK centers have recently engaged in the provision of data, with a database of contacts available for centers, all of which should improve the feasibility of conducting the study.

### Challenges

A positive response to BAS treatment is considered here as the gold standard for the diagnosis of BAM; a negative response will be coded as the patient not having BAM. However, this assumes that BAS is always effective in patients suffering from BAM. Without further research, it is impossible to assess whether this is a realistic claim. Similarly, it is possible that patients may have a placebo response (ie, an improvement in clinical symptoms even if they do not have underlying BAM). Longer-term follow-up may help to assuage these concerns.

Some forms of BAS treatment are unpleasant and poorly tolerated, including cholestyramine and colestipol, due to the texture and taste of the resin powder. This may reduce both the willingness of patients to take part in the study and adherence to treatment once started. Recruitment may also be affected by the fact that *all* patients will receive BAS regardless of whether SeHCAT indicates any likely benefit. However, in this regard, maintaining blindness to the SeHCAT result should help to retain participants once they have agreed to take part. These issues could be surmounted by using the drug colesevelam, which is available in tablet form and is well tolerated. However, colesevelam has not been assessed in randomized controlled trials for the treatment of BAM and is not currently licensed in the United Kingdom for this purpose [19].

Conducting a prospective multicenter study presents its own challenges, which include potential variation in procedures and in data quality between centers and the need for effective management of centers to ensure study timelines are achieved. To address these challenges, standardized protocols will be developed for the administration of the SeHCAT test and the laboratory assessment of biomarkers, and definitions will be agreed for all clinical assessments, including those required to assess patient eligibility and response to treatment. A consistent approach will be developed for communicating to patients the potential benefits as well as adverse effects of BAS treatment to encourage optimum treatment adherence. The study manager will be responsible for liaising with centers to ensure that agreed procedures are observed, that patients are recruited and followed up, and that data are complete and uploaded to the database in a timely fashion.

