The patient will be requested to return to the Nuclear Medicine Department on day 7 to undergo a second scan to measure the retention of SeHCAT, thus completing the test. The SeHCAT test result will be concealed from the clinician and the patient until the 2-week follow-up appointment. On the visit to complete the SeHCAT test, BAS will be dispensed to allow the patient to commence treatment on the following day. BAS will be prescribed to all patients according to a standard protocol based on current clinical practice.

All patients will attend a follow-up appointment with the gastroenterologist 2 weeks after the initiation of treatment with BAS. A clinical assessment will be performed to capture the relevant outcome measures: the patient’s adherence to treatment, improvement of symptoms, and quality of life (QoL). The QoL assessment will be undertaken by a research nurse trained in qualitative methodology. The clinical assessment will determine whether there has been a positive or negative response to BAS treatment. A standardized definition will be agreed for the degree of improvement in symptoms required to represent a positive response to treatment. At the follow-up appointment, the SeHCAT test result will be revealed to the clinician and the patient. A positive response to treatment at 2 weeks with evidence of treatment adherence will be used as the gold standard that defines a diagnosis of BAM.

Patients with a negative response to treatment will stop BAS treatment promptly (irrespective of SeHCAT test result) and may be directed to other investigations. At this stage, blood and fecal samples will be collected from this group for assessment of biomarkers. Patients with a positive response to BAS treatment (irrespective of SeHCAT test result) will continue on BAS treatment for a further 2 weeks. For this group, a second follow-up appointment will be performed at 4 weeks to repeat the outcome assessment. At this second follow-up visit, blood and fecal samples will be collected for further biomarker testing.

At 8 weeks, all patients entered into the study will be contacted for a telephone follow-up appointment to collect final follow-up data. Any interventions other than those included in the study protocol will be recorded during the study period.

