### Sample Size

Sample size was calculated based on the 95% confidence intervals of the sensitivity and specificity of the SeHCAT test result in predicting true BAM as defined by response to BAS treatment [16]. The prevalence of BAM in this population of patients attending gastroenterology appointments with chronic diarrhea is estimated to be approximately 50% [6]. Assuming a minimum value of 70% for either sensitivity or specificity [7], a sample of 600 patients (and therefore 300 true positives) would give an acceptable 95% confidence interval of 65% to 75%. Sensitivities or specificities closer to 1 will have narrower confidence intervals. If the assumption of 50% true positives is incorrect, an alternative scenario of 3:1 positives to negatives would give a 95% confidence interval of 62% to 77% around a specificity of 70%.

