### Statistical Analysis

Results of the SeHCAT test (percentage retention per patient) will be presented using suitable descriptive methods, including frequencies, proportions, means, and standard deviations, as appropriate. Response to BAS treatment will be presented as a proportion of those who initiated the treatment. All descriptive statistics will be presented with 95% confidence intervals.

The diagnostic accuracy of the SeHCAT test to provide a positive indication of BAM compared with the gold standard of a positive response to BAS at 2 weeks of treatment adherence will be investigated using the receiver operating characteristic (ROC) curves approach to compare different choice of thresholds. Sensitivity, specificity, positive predictive value, negative predictive value, likelihood ratios, and area under the curve will be calculated and presented with 95% confidence intervals. Multivariable logistic regression models will be used to assess the association between presence of BAM and continuous SeHCAT retention levels after adjustment for confounders.

Similar methods will be used to assess the diagnostic accuracy of biomarkers in the prediction of BAM. The diagnostic accuracy of the selected biomarkers will be compared to that of the SeHCAT test using the McNemar test for paired proportions.

Where diagnosis of BAM is confirmed, the association between severity of BAM (as assessed clinically at baseline) and the continuous SeHCAT result will be investigated using appropriate multivariable regression models taking into account prognostic baseline variables as potential confounders.

The EQ-5D scores [15] will be derived using standard procedures and will be used to describe the QoL of different subgroups. The change in QoL for the SeHCAT-positive group who respond positively or negatively to BAS will be examined and compared using regression methods adjusting for prognostic variables including QoL at baseline.

All analyses will be 2-sided with 5% significance level and will be reported according to the international standards for the reporting of diagnostic accuracy studies [17].

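### The reference standard is worded inconsistently for patients who do not take the sequestrant; read naturally, non-adherent BAM patients who do not improve count as disease-free, biasing specificity, PPV and NPV by an amount that depends on an unstated non-adherence rate

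*Protocol article*

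**What the plan says.** Three sections of the protocol article bear on who counts as having BAM.

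- Study Procedure and Outcome Measures sets a two-part condition: "A positive response to treatment at 2 weeks with evidence of treatment adherence will be used as the gold standard". The same section allows only two outcomes: "The clinical assessment will determine whether there has been a positive or negative response to BAS treatment".
- Statistical Analysis compares SeHCAT with the "gold standard of a positive response to BAS at 2 weeks of treatment adherence". It does not say what happens to patients who did not adhere. For the descriptive summary, "Response to BAS treatment will be presented as a proportion of those who initiated the treatment".
- Challenges treats response alone as deciding the matter: a positive response is the gold standard, and "a negative response will be coded as the patient not having BAM".

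Challenges also expects tolerability problems with the resin powders: "This may reduce both the willingness of patients to take part in the study and adherence to treatment once started". That remark is about recruitment and retention. The limits it concedes for the reference standard are imperfect drug efficacy and placebo response; misclassification through non-adherence is not among them.

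**The concern.** A trial of treatment can rule BAM out only in a patient who took the treatment. If someone with BAM does not take the sequestrant and stays symptomatic, the reference standard has not been applied, yet the stated coding makes that person a non-case. Such a patient with low SeHCAT retention becomes a false positive; one with normal retention becomes a true negative. The test then looks less specific because the drug was not taken, not because the test erred.

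The label defines disease status for the primary objective. The ROC curves, the choice of cut-off, the biomarker comparisons and the logistic models all use it. A larger sample would not remove the error. Later follow-up within this design would not settle it either, because negative responders stop the sequestrant at the 2-week visit.

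**Working it through.** **Reading the sections together.** The four combinations of adherence and response are classified as follows.

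| Patient | Study Procedure | Challenges |
|---|---|---|
| Adherent, responded | BAM | BAM |
| Adherent, no response | not BAM | not BAM |
| Not adherent, no response | negative response; no separate class | not BAM |
| Not adherent, improved | fails the adherence condition | BAM |

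The last two rows are the problem. The third is a definite label without a valid reference test; the fourth is a contradiction.

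**Inputs.** From Sample Size: 600 patients, prevalence π that "is estimated to be approximately 50" per cent, a minimum of 70% for sensitivity (Se) or specificity (Sp), and a planned interval of 65% to 75%. Assumed: a share d of true BAM patients does not adhere, does not improve and is coded as not BAM, with d the same whatever the SeHCAT result. The article gives no value for d; 5% to 30% is used as a range.

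**The plan's own figure.** With 300 per class, 1.96 × √(0.7 × 0.3 / 300) = 0.0519, giving 64.8% to 75.2%. This reproduces the stated 65% to 75%. The half-width is 5.2 points.

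**Cells under the stated coding.** TP = π·Se·(1−d); FN = π·(1−Se)·(1−d); TN = (1−π)·Sp + π·(1−Se)·d; FP = (1−π)·(1−Sp) + π·Se·d.

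At π = 0.5 these give:

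- Sensitivity: the factor (1−d) cancels, so there is no change.
- Specificity: bias = −d(Se + Sp − 1)/(1 + d).
- PPV: the number testing positive is unchanged and true positives shrink by (1−d), so bias = −d·PPV.
- NPV: bias = +d(1 − NPV).

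**At 70/70, where PPV and NPV are also 70%:**

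| d | Specificity | PPV | NPV |
|---|---|---|---|
| 5% | 68.1% (−1.9) | 66.5% (−3.5) | 71.5% (+1.5) |
| 10% | 66.4% (−3.6) | 63.0% (−7.0) | 73.0% (+3.0) |
| 15% | 64.8% (−5.2) | 59.5% (−10.5) | 74.5% (+4.5) |
| 20% | 63.3% (−6.7) | 56.0% (−14.0) | 76.0% (+6.0) |
| 30% | 60.8% (−9.2) | 49.0% (−21.0) | 79.0% (+9.0) |

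**Where the bias reaches 5.2 points.** Specificity: 0.4d/(1+d) = 0.0519, so d = 0.0519/0.3481 = 14.9%. PPV: d = 0.0519/0.7 = 7.4%. NPV: d = 0.0519/0.3 = 17.3%.

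**A more accurate test.** The Introduction reports specificity above 0.9 in three small trial-of-treatment studies, and sensitivity of 0.67 to 0.95 in the two that used an 8% cut-off. The specificity bias grows with Se + Sp − 1. At 67/90, d = 0.0519/(0.57 − 0.0519) = 10.0%. At 80/95, d = 0.0519/(0.75 − 0.0519) = 7.4%, and apparent specificity is 88%, 83% and 78% at d = 10%, 20% and 30%. NPV behaves the other way: at 90/90 its bias reaches its own half-width of 3.4 points only at d of about 34%.

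**If non-adherence does depend on SeHCAT.** At 70/70, with d = 10% in test-positive and 30% in test-negative BAM patients, apparent sensitivity is 0.315/(0.315 + 0.105) = 75%. Reversed, it is 0.245/(0.245 + 0.135) = 64.5%.

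**The case against.** The strongest reply is that no sentence says non-adherers are coded as not having BAM. The coding sentence sits in a Discussion paragraph on efficacy and placebo response, while Methods ties the reference standard to adherence. The Statistical Analysis wording can be read as confining the accuracy analysis to adherent patients, and the denominator of treatment initiators is descriptive only. Handling of non-adherers could also be settled in a full protocol or analysis plan that is not shown. This stands as far as it goes: the coding of non-adherers is inferred. But the article does not merely omit detail. It states a rule for negative responses that makes no reference to adherence, and its sections disagree about a non-adherer who improves.

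A reader might infer that the bias exceeds the planned confidence half-width whatever happens. The documents do not support that. No non-adherence rate is given; at d = 10% and 70/70 only PPV moves by more than 5.2 points. The planned interval also covers sensitivity and specificity alone. That 5.2 points fits PPV and NPV too is a coincidence of the planning case, where 300 patients test positive and 300 negative.

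The model may also overstate d. The Introduction says adherent patients respond within days, so some who take part of the course may have improved. People unwilling to take the sequestrant are excluded, and a communication plan and concealment of the result are meant to support adherence and retention. These points lower the plausible d; they do not repair the coding.

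**Conclusion.** The concern holds in conditional form. The reference standard is defined inconsistently across the three sections, and its natural reading places non-adherent, unimproved BAM patients among the disease-free. The direction of bias (specificity and PPV down, NPV up, sensitivity unchanged) rests on non-adherence being unrelated to the SeHCAT result. Concealing that result until the 2-week visit makes this plausible but does not guarantee it.

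The size rests on an assumed rate. At the planning values, all three measures are off by more than 5.2 points only above about 17% non-adherence among BAM patients. If the test is as specific as the earlier small studies suggest, specificity is affected at lower rates. It does not follow that the planned precision is necessarily swamped, nor that the article says outright that non-adherers are negative. The wording should still be corrected before the study starts, because it fixes the outcome of the primary analysis.

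**What to change.** Reconcile Study Procedure and Outcome Measures, Statistical Analysis and Challenges, and replace the coding sentence with three reference-standard states, using the adherence data already collected at 2 weeks:

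- BAM-positive: adherent and responded.
- BAM-negative: adherent and did not respond.
- Undetermined: not adherent, or not assessed at 2 weeks.

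Estimate accuracy in the determinate patients. Beside it, report an analysis that multiply imputes the undetermined group from BAM type, baseline symptoms, SeHCAT retention and biomarkers, and the result under the present coding.

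Cost: wording changes and one imputation analysis, with no new data, since funding is still being sought and the study has not begun. Precision falls: with 20% undetermined, the half-width at 70% goes from 5.2 to 5.8 points (factor √(1/0.8) = 1.12, about 12% wider). Keeping 600 assessable patients would need 600/0.8 = 750 enrolled.

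The determinate-patient analysis has its own weakness. PPV and NPV stay biased if non-adherence depends on BAM status or on early lack of benefit. For example, assume 10% undetermined among BAM and 30% among non-BAM patients at 70/70 and 50% prevalence. Prevalence among assessable patients becomes 0.45/(0.45 + 0.35) = 56%, PPV 0.315/(0.315 + 0.105) = 75% and NPV 0.245/(0.245 + 0.135) = 64.5%. Imputation reduces this but does not remove it, which is why the three results should be shown together.

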### Future Directions

The results from this study will need to be validated in other populations in the future. Populations with different dietary content, such as proportion of fiber, may react differently to the SeHCAT test [8]. Analysis of the variation in SeHCAT results between different centers will give an indication of the extent to which population-specific approaches may be required.

Depending on the results found for the 2 biomarkers considered, other biomarkers may be worth investigating as well as the potential for combining the SeHCAT and biomarker results.

## Abbreviations

C4: 7-alpha-hydroxy-4-cholesten-3-one
ARSAC: Administration of Radioactive Substances Advisory Committee
BAM: bile acid malabsorption
BAS: bile acid sequestrant
ELISA: enzyme-linked immunosorbent assay
FGF-19: fibroblast growth factor 19
KiTEC: King’s Technology Evaluation Centre
NIHR: National Institute for Health Research
QoL: quality of life
SeHCAT: tauroselcholic (selenium-75) acid
